### Radiological assessment

Radiological assessment included CT, MRI, anterior-posterior position, lateral position, flexion and extension position lumbar X-ray.

The lumbar spinal stenosis grade of central canal stenosis [19], lateral recess stenosis [20], and foraminal stenosis [21] was evaluated on MRI. The stenosis grade was divided into mild, moderate, and severe.

The degeneration grade of intervertebral disc of operative level and adjacent level was accessed on MRI according to Pfirrmann grade [22].

The decompression range (including the maximum sagittal diameter of the axial spinal canal, lateral recess angle, lateral recess sagittal diameter, disc height, and volume of bone resected, and etc.) was measured on CT [23, 24].

The range of motion (ROM) of operative level and adjacent level was measured by the Cobb angle of function spinal unit (FSU) on flexion and extension position X-ray [25].

### Outcome measures

#### Primary outcome measure

The primary outcome measure is the score changes of ODI between baseline and 12-month follow-up.

#### Secondary outcome measures

The secondary outcome measures are:The score changes between baseline and 3 months, 6 months, 12 months follow up in: JOA, and VAS.The MacNab criteria of 3 months, 6 months, 12 months follow up. The complication rate and patient satisfaction rate before discharged, and at 3 months, 6 months, 12 months follow up.The changes between baseline and 3 months, 6 months, 12 months follow up in: degeneration grade of adjacent level, stenosis grade of operative level, ROM of operative level and adjacent level.The relationship between the exposure measures, special measures and the postoperative clinical outcomes. (SPIRIT 12)

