## Background

Lumbar spinal stenosis (LSS) is caused by the degeneration of the lumbar spine including disc herniation, the hypertrophy of facet joint and ligamentum flavum, and the formation of osteophyte [1]. The characteristics of LSS are low back pain, sciatica, and intermittent claudication which will seriously affect the daily life and work of patients [1, 2].

LSS is the most frequent indication for spine surgery among the elderly population [3, 4], and previous studies have demonstrated that surgical treatment was better than conservative treatment in selected patients [5, 6].

Open decompression and fusion was the most common treatment and used to be regarded as the golden standard treatment for LSS [7, 8]. However, due to the surgical trauma caused by open decompression and fusion surgery, complications, and the acceleration of adjacent level degradation, more minimally invasive treatments were required [9–11].

Percutaneous endoscopic decompression is a minimally invasive treatment which has the advantage of operated under local anesthesia, less surgical trauma, fewer complications, shorter hospital stay, and rapid postoperative recovery. The application of percutaneous endoscopic decompression has been limited to soft disc herniation. In recent years, with the development of endoscopic instruments and surgical techniques, some surgeons applied percutaneous endoscopic decompression for the treatment of LSS [12–14]. However, the related studies had some limitations including small sample size, short-term follow-up, single-center, no control group, retrospective study which reduced the quality of evidence for the conclusion. (SPIRIT 6a,b).

The present prospective, multicenter, large sample size cohort study based on real-world will be helpful for the evaluation of the clinical effectiveness and safety of the percutaneous endoscopic decompression for LSS. Furthermore, we designed to analyze various influence factors for the prognosis of LSS including degeneration grade, pathology type, stenosis grade, decompression range. The present study will provide useful information for the development of guidelines and standards for percutaneous endoscopic decompression for the treatment of LSS.

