## Methods

### Aim and objective

The primary aim of this study is to compare the effectiveness and safety of percutaneous endoscopic decompression surgery and open decompression and fusion surgery for the treatment of patients with LSS in the real-world treatment setting. The secondary aim is to investigate the prognosis factors for LSS treated by surgery.

The objectives of this study:Compare the clinical outcomes of percutaneous endoscopic decompression and open decompression and fusion for lumbar spinal stenosis.Investigate the influence of various factors (including demographic variables, risk factors, treatment factors, and radiological assessment) for the clinical outcome of LSS treated by surgery.Investigate the influence of percutaneous endoscopic decompression surgery on stability of the operated level.Investigate the influence of percutaneous endoscopic decompression surgery on degeneration of adjacent level. (SPIRIT 7)

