### Sample size calculation

The sample size calculation was based on the ODI score at 12 months follow-up. According to the retrospective study of our center and previous literature reported [15], the mean value and standard deviation of ODI score in 12 months after surgery was 20 and 15 in the percutaneous endoscopic decompression group, and 15 and 10 in the open decompression and fusion group. Assuming an overall type 1 error (α) of 0.05 and type II error (β) of 0.1, we needed 137 patients in each group to detect the difference of ODI in two groups. Considering the final follow-up rate of 80% and the center effect value of 1.2, a minimum of 206 patients were needed in each group. Moreover, this study is a real-world observation study, it is necessary to consider confounding factors when analyzing the results. We estimated that 300 patients in each group will be enrolled in this study. (SPIRIT 14).

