### Follow up

Patients will be followed up at 3, 6, 12 months after surgery. Clinical and radiological assessment at 3 and 12 months after surgery will be performed through outpatient follow-up. Clinical assessment at 6 months after surgery will be completed through email or telephone (Table 1). Adverse events will be recorded during the follow-up period. (SPIRIT 13, 18b).

**Table 1 Tab1:** Data collection

Variables	Baseline	Perioperative	3 months	6 months	12 months
Demographic Variable					
Age	X				
Gender	X				
BMI	X				
Ethnicity	X				
Center of residence	X				
Risk Factors					
Comorbidity	X				
Smoking status	X				
Previous spinal surgery	X				
Pathology types	X				
Affected level	X				
Symptoms duration	X				
Degeneration grade	X				
Stenosis grade	X				
Treatment Factors					
Operation approach		X			
Operative time		X			
Bleed loss		X			
Postoperative hospital stay		X			
Surgeon		X			
Radiological Assessment					
X-ray	X		X		X
CT	X		X		X
MRI	X		X		X
Clinical Assessment					
VAS (back & leg)	X	X	X	X	X
ODI	X		X	X	X
JOA	X		X	X	X
MacNab criteria			X	X	X
Patient satisfaction		X	X	X	X
Complications		X	X	X	X

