### Measures

#### Exposure measures

The exposure measures include demographic variables, risk factors and treatment factors. The demographic variables included age, gender, BMI, ethnicity, and center of residence. The risk factors were composed of healthcare variables (Comorbidity, smoking status, previous spinal surgery), and symptom related variables (Pathology types, affected level, symptoms duration, degeneration grade, stenosis grade). The treatment factors included operation approach, operative time, bleed loss, postoperative hospital stay, surgeon. The demographic variables, and risk factors were collected after patients were enrolled in the study, and before the surgery was performed. The treatment factors were collected before patients were discharged. (Table 1).

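### The pre-discharge complication rate is counted over a window that the protocol expects to be shorter after endoscopic surgery, so with equal true risk this early rate favours the endoscopic group

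*Protocol article*

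**What the plan says.** The Secondary outcome measures section of the protocol article names "The complication rate and patient satisfaction rate before discharged, and at 3 months, 6 months, 12 months follow up". Table 1 (Data collection) matches this: complications and patient satisfaction are both marked in the perioperative column and again at 3, 6 and 12 months. No number of postoperative days is attached to the first time point.

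The Background section describes endoscopic decompression as having "less surgical trauma, fewer complications, shorter hospital stay, and rapid postoperative recovery". The Exposure measures section shows that length of stay is recorded for each patient: "The treatment factors included operation approach, operative time, bleed loss, postoperative hospital stay, surgeon".

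Safety belongs to the primary aim, which is to "compare the effectiveness and safety of percutaneous endoscopic decompression surgery and open decompression and fusion surgery" (Aim and objective). The Follow up section adds that "Adverse events will be recorded during the follow-up period".

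**The concern.** A rate that closes at discharge has an observation time that the treatment itself influences. Take a complication that appears on postoperative day 5. It counts for an open-surgery patient who is still in hospital and does not count for an endoscopic patient who is already at home. On the protocol's own expectation about stay, the early window is shorter in one group.

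The stake is one named safety outcome. Fewer complications is among the advantages that the Background attributes to the endoscopic technique, and this measure leans towards that answer before any patient is treated. Adjustment for baseline confounders would not help, because the problem is unequal observation time and not selection. Adjustment for length of stay would not be a clean repair either: stay follows from the treatment, and a complication can prolong it.

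**Working it through.** **The plan's own figures.** The article computes nothing for complications. Its only calculation is the sample size for the Oswestry Disability Index (ODI), and it reproduces: (1.960 + 1.282)² × (15² + 10²) / 5² = 136.6, so 137 per group; 137 × 1.2 / 0.80 = 205.5, so 206. Nothing below depends on it except the planned enrolment of 300 per group.

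**Inputs from the document.** The early window ends at discharge (Secondary outcome measures). Stay is expected to be shorter after endoscopic surgery, with no days given (Background). There are 300 patients per group (Sample size calculation).

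**Assumed inputs, because the document gives none.** The true 30-day risk R is the same in both groups. Stays (endoscopic vs open) are 1 vs 4, 2 vs 5, 2 vs 7 and 3 vs 7 days. Event timing follows one of three patterns, where t is the day of discharge:

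- Constant hazard: rate = 1 − exp(−ht), with h = −ln(1 − R)/30.
- Front-loaded: rate = R × F(t), with F(t) = (1 − exp(−t/5)) / (1 − exp(−6)).
- Half on the day of surgery, the rest front-loaded: rate = R × (0.5 + 0.5 F(t)).

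**One case in full: R = 10%, stays of 2 vs 5 days.** F(2) = 0.330 and F(5) = 0.634.

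- Constant: 0.70% vs 1.74%, risk ratio 0.40.
- Front-loaded: 3.3% vs 6.3%, risk ratio 0.52. The standard error is √(0.033 × 0.967/300 + 0.0634 × 0.9366/300) = 0.0174, so the expected z is 0.0304/0.0174 = 1.74 and the chance of p < 0.05 from the artefact alone is about 41%.
- Half on the day of surgery: 6.7% vs 8.2%, risk ratio 0.81. The standard error is 0.0214, the expected z is 0.0152/0.0214 = 0.71, and the chance is about 11%.

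**All stays, R = 10%.** RR is the risk ratio, endoscopic over open; the percentages are the chance of p < 0.05 with 300 per group.

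| Stays (days) | Constant: RR | Front-loaded: RR, chance | Half on day of surgery: RR, chance |
|---|---|---|---|
| 1 vs 4 | 0.25 | 0.33, 68% | 0.76, 14% |
| 2 vs 5 | 0.40 | 0.52, 41% | 0.81, 11% |
| 2 vs 7 | 0.29 | 0.44, 63% | 0.76, 16% |
| 3 vs 7 | 0.43 | 0.60, 34% | 0.83, 10% |
| equal | 1.00 | 1.00 | 1.00 |

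For R between 5% and 15%, the chance of p < 0.05 is 19% to 85% when events are front-loaded and 7% to 23% when half occur on the day of surgery. The risk ratios hardly change with R.

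**A simpler check.** Spread a 10% risk evenly over 10 days. Stays of 3 vs 8 days give 3% vs 8%, with standard error √(0.03 × 0.97/300 + 0.08 × 0.92/300) = 0.0185 and z = 2.7. Stays of 5 vs 7 days give 5% vs 7%, with standard error 0.0194 and z = 1.03. The first pair is near the worst case: the stays differ greatly and no events cluster around the operation.

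**With a common window.** If both groups are counted from surgery to the same day and the true risk is equal, the risk ratio is 1.00 under every timing pattern.

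**The case against.** The best defence is that few events need be lost. Complications are collected again at 3, 6 and 12 months and adverse events are recorded during follow-up, so a day-5 event at home has a place to go. This stands, and it confines the bias to the early rate. The one gap is that the article does not say whether the 3-month rate counts from surgery or only from discharge. If it counted only from discharge, the same day-5 event would fall in different rates in the two groups.

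It can also be said that the sentence is a collection schedule, and that the Statistical analysis section names no between-group test of the pre-discharge rate. That is fair as to analysis, which an unseen document may settle. But the section presents the rate as an outcome in its own right, in a study whose purpose is to compare the two groups, and its end point is fixed there.

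Third, events during or on the day of surgery are captured equally in both groups. This stands too: it moves the risk ratio towards 0.76 to 0.83 in the illustration, without removing the bias.

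A reader might infer more than the document supports in three ways. One is that the whole safety comparison is tilted; the later common time points argue against that. Another is that satisfaction at discharge is biased towards endoscopy; the ratings are taken at different postoperative times, but nothing fixes the direction, and a satisfaction score does not accumulate with time as events do. The third is that the sentence "The treatment factors were collected before patients were discharged" confirms the window for complications; it concerns approach, operating time, blood loss, stay and surgeon, and not when complications are counted.

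**Conclusion.** The point holds for the pre-discharge complication rate alone. The direction is settled, given the shorter endoscopic stay that the protocol expects, equal true risk over time, and at least some events arising between the two typical discharge days. The size is not settled: spurious risk ratios run from about 0.25 to about 0.83 under the assumed stays and timing, and the bias vanishes if stays are equal. The 3-, 6- and 12-month complication rates are untouched, provided they count from the day of surgery, and so is the primary ODI outcome. For satisfaction, all that can be said is that the discharge ratings are not taken at comparable times.

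**What to change.** Make the early between-group comparison the complication rate cumulative from the date of surgery to the 3-month visit, with the same window in both groups, and state that the 6- and 12-month rates also count from surgery. Record the onset date of each event; the case report form is not shown and may already do so. Report in-hospital complications descriptively beside length of stay, which is already collected. Rest the satisfaction comparison on the 3-, 6- and 12-month ratings, noting that the discharge rating comes at different postoperative times in the two groups.

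The cost is a change of wording and perhaps one date field, with no new visit. A 30-day window would be less convenient, since Table 1 has no contact at that time. A small downside remains: early events at home rely partly on recall at 3 months, while longer-stay patients are observed directly, so some under-recording in the group discharged earlier may persist, in the same direction as the present bias.

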#### Special measures

The special measures were composed of clinical assessment and radiological assessment.

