### Clinical assessment

Visual analogue score (VAS) [16], Oswestry disability index (ODI) [17], Japanese Orthopaedic Association score (JOA) [18], MacNab criteria, Patient satisfaction, Complications.

VAS divided the degree of pain from 0 to 10. 0 represented no pain, and 10 represented the most pain. VAS was used to evaluate the pain of the back and lower limb separately.

ODI was wildly used to evaluate the limitations of daily activities caused by spinal diseases. The simplified Chinese version ODI was composed of 10 questions, including pain intensity, self-care, lifting, walking, sitting, standing, sleep, sex, social, travel. The score range for each question was 0–5 points. Summarized each question patient answered and converted into a percentage score.

JOA was an effective method to assess lumbar diseases and the recovery of lumbar spine surgery. The simplified Chinese version JOA included five aspects: low back pain (four items), lumbar function (six items), walking ability (five items), social life function (four items), and mental health (seven items). The recovery rate was calculated according to preoperative and postoperative JOA.

MacNab criteria were used to access the overall effectiveness of the surgery, including four grades: excellent, good, fair, poor.

Patient satisfaction was the patient’s subjective impression of surgery, including three grades: satisfied and accept, not satisfied but accept, not satisfied, and not accept.

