## Discussion

The goal of this study is to evaluate the real-world effectiveness and safety of percutaneous endoscopic decompression surgery versus open decompression and fusion surgery for LSS. Moreover, we also planned to investigate the influence of various factor on clinical outcomes of LSS.

Percutaneous endoscopic decompression is an advanced mini-invasive technique. Sun et al. [14] introduced an interlaminar approach endoscopic decompression technique to treat lumbar central canal stenosis, the primary outcomes of 38 patients was satisfying.

Lee et al. [12] analyzed 213 patients with lumbar canal stenosis or lateral recess stenosis treated by percutaneous endoscopic decompression, the outcomes of 26 months follow-up showed the satisfied rate reached to 93.8%.

However, there have been some concerns about the application of the percutaneous endoscopic decompression for LSS. The first concern is whether the percutaneous endoscopic decompression could provide sufficient decompression without affecting the stability of the operative level. Secondly, whether the percutaneous endoscopic decompression prevents the degeneration of adjacent level. Finally, the recurrence of symptoms its influence factors.

In this study, the dynamic X-ray, CT, and MRI were performed preoperatively and at 3, 12 months follow-up. The instability of operative level will be assessed according to the changes of ROM and VAS (back) [25]. The decompression range and the degeneration grade will be also measured. These will clarify the exact influence of percutaneous endoscopic decompression on the stability of operative level and the degeneration of adjacent level. Furthermore, various influence factors including demographic variables, healthcare variables, symptom related variables, treatment factors, degeneration grade, stenosis grade, decompression range, stability of operative level, and degeneration of adjacent levels were evaluated. The relationship between these various influencing factors and clinical effectiveness will be helpful to solve the controversial issues of percutaneous endoscopic decompression treatment for LSS.

To the best of our knowledge, this is the first prospective, multicenter, large sample study comparing endoscopic decompression and open decompression fusion treatment for LSS which incorporated clinical evaluation, dynamic X-ray, CT, and MRI.

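### Stability and adjacent-level findings from follow-up imaging are treated as influencing factors without time order, and instability is defined partly by an outcome score, so these associations cannot be called prognostic

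*Protocol article*

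**What the plan says.** The last item under Secondary outcome measures is "The relationship between the exposure measures, special measures and the postoperative clinical outcomes". No time point is given for the measures or for the outcomes.

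The Special measures section reads "The special measures were composed of clinical assessment and radiological assessment". The Clinical assessment section then lists VAS, ODI and JOA, followed by "MacNab criteria, Patient satisfaction, Complications". These are the instruments that supply the study's clinical outcomes. On timing, Follow up says "Clinical and radiological assessment at 3 and 12 months after surgery will be performed through outpatient follow-up"; clinical scores are also collected at 6 months, by email or telephone.

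The Discussion ends its list of influence factors with "degeneration grade, stenosis grade, decompression range, stability of operative level, and degeneration of adjacent levels were evaluated" and says that the relation of these factors to clinical effectiveness will be studied. Just before that, it explains that instability of the operated level will be judged from the change in ROM together with the change in back VAS.

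The exposure measures, by contrast, do have a time limit: "The demographic variables, and risk factors were collected after patients were enrolled in the study, and before the surgery was performed". Treatment factors are fixed before discharge.

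**The concern.** The article's secondary aim is to find prognostic factors for surgically treated stenosis. A prognostic factor has to be known before the outcome it is said to predict, and it must not contain that outcome. The plan breaks both conditions for some of the factors it names.

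- **Time order.** A finding on the 12-month film cannot predict a score taken at that visit or earlier. The association may also run the other way: a patient in pain may move less on the flexion-extension film, so a smaller ROM can be a consequence of a poor result and not its cause.
- **Shared content.** A stability variable that includes change in back VAS will correlate with change in VAS by construction, whatever the spine is doing.

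The Background says that the study should inform guidelines and standards for endoscopic decompression. Labelling such associations as influence factors would invite readers to act on them.

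**Working it through.** No figure in the plan bears on this point, so the check is mainly a comparison of definitions and timings.

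**Step 1. When each item is available** (Table 1, Exposure measures, Radiological assessment, Discussion)

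| Item | Time | Usable as a predictor of 12-month ODI? |
|---|---|---|
| Demographic variables and risk factors, including degeneration and stenosis grade | Before surgery | Yes |
| Treatment factors | Before discharge | Yes |
| Baseline VAS, ODI, JOA and imaging | Before surgery | Yes |
| X-ray, CT, MRI at 3 months | 9 months before the outcome | Yes, among patients assessed at 3 months |
| X-ray, CT, MRI at 12 months | Same visit | No, association only |
| MacNab, satisfaction, complications | No baseline value; recorded after surgery only | Not at the same visit |
| Instability from ROM and back VAS | Follow-up; no visit named | Contains an outcome score |

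The secondary outcome list also mentions 6 months for imaging changes, but Table 1 and Follow up show no imaging then. Table 1 is used here.

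**Step 2. Order against the outcomes.** For the primary outcome, the plan says "The primary outcome measure is the score changes of ODI between baseline and 12-month follow-up". The 12-month films are concurrent with it. Against the 3- and 6-month secondary outcomes they are late by 12 − 3 = 9 months and 12 − 6 = 6 months. One of the two postoperative imaging visits is therefore never earlier than any outcome.

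**Step 3. Could special measures mean baseline values only?** This does not fit the definition. MacNab, satisfaction and complications have no baseline value in Table 1; indeed "MacNab criteria were used to access the overall effectiveness of the surgery". Decompression range includes the volume of bone removed, which exists only after surgery. Stability and adjacent-level degeneration are framed in the objectives as effects of the operation.

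**Step 4. Circularity.** Change in VAS is a secondary outcome, and change in back VAS is part of the instability assessment. By the article's own description of the instruments, ODI has a pain-intensity question and JOA a low back pain domain. The overlap is therefore direct for VAS and partial for ODI and JOA. The article does not say how ROM and VAS are combined, so the size of the overlap cannot be computed.

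**Step 5. Illustration only: what a concurrent score would do if it entered a model.** The correlations are assumed; none is in the document. Let a baseline factor x correlate 0.30 with 12-month ODI (y), and let z be a score from the same visit. The standardised coefficient of x after adding z is

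(r_xy − r_zy × r_xz) / (1 − r_xz²)

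| | r_zy = 0.5 | r_zy = 0.7 | r_zy = 0.8 |
|---|---|---|---|
| r_xz = 0.30 | 0.15/0.91 = 0.16 | 0.09/0.91 = 0.10 | 0.06/0.91 = 0.07 |
| r_xz = 0.10 | 0.25/0.99 = 0.25 | 0.23/0.99 = 0.23 | 0.22/0.99 = 0.22 |

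The factor falls from 0.30 to somewhere between 0.07 and 0.25. The loss depends heavily on how strongly the factor relates to the concurrent score.

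**The case against.** A reader might infer from the definitions that 12-month ODI will be regressed on 12-month MacNab or JOA. The documents do not support that. Wherever the article names its factors, follow-up scores are absent: the Background lists degeneration grade, pathology type, stenosis grade and decompression range; the second objective lists demographic, risk, treatment and radiological factors; the Discussion list is similar. The secondary outcome speaks of a relationship and specifies no model. So the wording permits this use without showing an intention to make it, and the table in step 5 describes a model that the article does not describe. Nor does the article expressly pair 12-month films with 3- or 6-month outcomes; it only leaves that pairing open.

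It can also be said that candidate predictors and their time points usually belong in an analysis plan, which is not shown, and that relating follow-up imaging to clinical state is a fair descriptive question under the stability and adjacent-level objectives. Both are true in general. But the article does more than leave out timing. It names postoperative stability and adjacent-level degeneration as influencing factors, and it builds instability partly from an outcome score. Those are statements in the text, and an analysis plan that followed them would inherit the problem.

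Finally, time order alone would admit some postoperative scores, such as perioperative VAS or 3-month ODI, as predictors of the 12-month outcome. That is correct, so the exclusion needed is of scores taken at the same visit as the outcome or later.

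**Conclusion.** The point holds for imaging and stability. The article treats follow-up findings as influences on clinical effectiveness without requiring that they precede the outcome, and its instability measure contains change in back VAS. Associations found this way are partly circular and cannot be called prognostic. For the clinical scores, the point is narrower: the definitions of special measures and of the secondary outcome should be tightened because they allow follow-up scores as predictors, not because the article plans to use them.

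The conclusion about timing and circularity rests on the article's text alone. The size of any distortion is not known; the range 0.07 to 0.25 against 0.30 rests on assumed correlations and shows a mechanism, not a forecast. The damage is confined to the secondary aim. The difference-in-difference comparison of ODI and the sample size do not depend on it.

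**What to change.** In Secondary outcome measures, and in the matching Discussion paragraph, limit the prognostic model to factors measured before the outcome:

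- Admit baseline scores, baseline imaging and operative factors.
- Admit 3-month imaging, including decompression range, only as a landmark predictor of the 12-month outcome among patients assessed at 3 months.
- When stability is used to predict a clinical score, define it by ROM alone, without back VAS.
- Exclude clinical scores recorded at the same visit as the outcome or later. Say explicitly whether any earlier postoperative score is a candidate, since time order alone does not settle that.
- Report 12-month imaging against 12-month scores as a cross-sectional association, and do not call it a prognostic or influence factor.

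This changes the wording and the list of model terms and needs no new data. The price is fewer candidate factors and a landmark analysis that omits patients without 3-month imaging.
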